#### Statistical methods—primary endpoint (ITT population)

The baseline characteristics of the enrolled subjects, HHs, and clusters will be summarized by treatment arm. Specifically, we will examine subject age and gender at the individual level; wall type and roof type, the presence of open eaves, # of windows, # of doors at the HH levels; and cluster population and baseline overall infection incidence at the cluster level.

The primary hypothesis on PE against the first-time malaria infection will be tested by comparing the hazard rates of first-time malaria infection between the SR and placebo arms upon the completion of the study in the ITT population via a cloglog model for the interval-censored time to event data. The model will include the treatment arm (SR vs. placebo), relevant baseline covariates, and a random effect that accounts for the dependency among data collected from the same cluster.

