#### Primary hypothesis on first-time malaria infection

The sample size determination on the required number of subjects (HHs) per cluster for testing the primary hypothesis is based on the hazard rate comparison in the proportional hazards regression model [36, 37]. With the following specifications: 1-sided type I error rate = 5%, true PE = 30%, a between-cluster CV of hazard rate = 44% (based on historical data collected from Kenya), one interim analysis for efficacy and non-binding futility with the O’Brien-Fleming error spending function when 50% of events have been collected then 1055 first-time malaria events will need to be observed to reach 85% power in testing the primary hypothesis on PE.

With a baseline first-time malaria infection hazard rate of 3.0 per person-year, 30 clusters per treatment arm, with 20 subjects (HHs) per cluster are expected to yield 1055 independent first-time malaria events within a 12-month follow-up period per cohort post randomization to yield 85% power. If, by the end of the 2-year study, 1055 independent malaria events are not reached, the study may extend until 1055 events are collected without inflating the type I error rate in the testing of the primary hypothesis. Factoring in a LTFU rate at 35%, the required sample size is 28 subjects (HHs) per cluster, which will be split in half between the two sequential cohorts with 14 subjects (HHs) per cohort per cluster.

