## Statistical methods

### Statistical methods for primary and secondary outcomes {20a}

#### Primary hypothesis

H_0_: SR does not reduce the first-time malaria hazard rate compared to placebo in Kenya.

H_1_: SR reduces the first-time malaria hazard rate compared to placebo (first-time malaria hazard ratio between SR and placebo is < 1; the expected hazard ratio is 70% or PE is 30%.

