##### PE analysis without baseline covariates

A PE analysis on the first-time and the overall infections will be also performed by removing all the baseline covariates from the cloglog models and keeping “intervention group” as the only covariate (in addition to visit, as a categorical predictor per the model assumptions and setup). The hazard ratios between SR and placebo will be provided, along with 2-sided 90% CIs.

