### Methods for additional analyses (e.g., subgroup analyses) {20b}

#### Temporality of PE effects

It is expected malaria incidence changes by seasonality (rainy vs dry) and year. To examine the temporality of malaria incidence rates and the PE effect, a supplementary analysis will be performed by adding the seasonality (Jun-Dec/wet/peak and Jan-May/dry/low) and year (1 and 2) and their interaction with intervention to the covariate list in the cloglog models used for analyzing the first-time and overall infections. The PE will be estimated by seasonality and year.

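### The primary first-infection model pools two cohorts enrolled a year apart without a cohort or year term, so it slightly understates protective efficacy if the years differ

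*Protocol article*

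**What the plan says.** All references are to the protocol article.

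- **Statistical methods, primary endpoint:** a complementary log-log (cloglog) model for interval-censored time to first infection. "The model will include the treatment arm (SR vs. placebo), relevant baseline covariates, and a random effect" for cluster. Neither cohort nor year is named.
- **PE analysis without baseline covariates:** treatment is the only covariate kept, "in addition to visit, as a categorical predictor per the model assumptions and setup". Visit is therefore the time axis.
- **Temporality of PE effects:** "It is expected malaria incidence changes by seasonality (rainy vs dry) and year". Season, year (1 and 2) and their interactions with treatment are then added to the covariate list, as a supplementary analysis.
- **Trial design and Participant timeline:** two cohorts of different children, one followed from August 2021 to July 2022 and the other from August 2022 to July 2023. All 60 clusters supply 14 core-area children to each cohort.

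**The concern.** A term that has to be added for the supplementary analysis was not on the primary list. As written, visit k of year 1 and visit k of year 2 appear to share one baseline hazard. Both cohorts start in August, so visit number roughly follows calendar month and takes up most of the seasonality. The difference between years is what stays unmodelled. The cluster random effect cannot absorb it, because every cluster contributes to both years.

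Balance of arms within each year does not protect a hazard ratio when the risk set is being used up, and here it is used up fast. At 3.0 first infections per person-year, 1 − exp(−3.0) = 95% of placebo children would be infected within 12 months if there were no between-cluster variation. The high-incidence cohort empties faster under placebo than under SR, so later visits compare arms with different mixes of years.

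At stake is the size of the headline estimate. The primary objective is to quantify protective efficacy (PE) as well as to demonstrate it, and the result goes to the WHO advisory group. The primary hazard ratio would also differ from the year-adjusted supplementary one for a purely technical reason.

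**Working it through.** **Inputs from the protocol.** Hazard ratio 0.70 ("the expected hazard ratio is 70% or PE is 30"); cluster variation ("a between-cluster CV of hazard rate = 44% (based on historical data collected from Kenya"); 1055 events and 85% power ("1055 first-time malaria events will need to be observed to reach 85% power in testing the primary hypothesis on PE"); placebo hazard and cluster numbers ("With a baseline first-time malaria infection hazard rate of 3.0 per person-year, 30 clusters per treatment arm, with 20 subjects (HHs) per cluster"); final one-sided boundary p < 0.04668.

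**Assumptions.** Equal cohorts; 13 four-week visits; constant hazard within a year; the year-to-year hazard ratio. The article's Study setting section cites incidence of 2.5 to 4.1 per person per year from one earlier study, a ratio of 4.1/2.5 = 1.64. It does not say that this is a between-year contrast, so it only sets a scale here.

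**Step 1: the stated design reproduces.** Var(log HR) = 4/1055 + 2 × 0.44²/30 = 0.00379 + 0.01291 = 0.01670, so SE = 0.1292. A two-look O'Brien-Fleming test at one-sided 5% has final z = 1.678, which gives interim p = 0.00882 and final p = 0.04668, as stated. Power at 1055 events is 86.3% ignoring the futility rule and 84.3% if it is always followed, against the stated 85%.

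**Step 2: the mechanism at six months.** Take placebo hazards of 4.0 and 2.0 in the two years, and SR hazards of 2.8 and 1.4.

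- Placebo still uninfected: exp(−2.0) = 0.135 and exp(−1.0) = 0.368. High-year share 0.135/0.503 = 0.269. Mean hazard 4.0 × 0.269 + 2.0 × 0.731 = 2.538.
- SR still uninfected: exp(−1.4) = 0.247 and exp(−0.7) = 0.497. High-year share 0.247/0.743 = 0.332. Mean hazard 2.8 × 0.332 + 1.4 × 0.668 = 1.865.
- Pooled hazard ratio at that point: 1.865/2.538 = 0.735, although it is 0.70 within each year.

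**Step 3: what the pooled model estimates.** Expected numbers at risk and infected, by arm and visit, were summed over the cohorts. A cloglog model with visit and arm was fitted by maximum likelihood, without cluster effects.

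| Placebo hazards, two years | Ratio | Pooled HR | Pooled HR, 35% dropout |
|---|---|---|---|
| 3.0 / 3.0 | 1.0 | 0.700 | 0.700 |
| 3.33 / 2.67 | 1.25 | 0.702 | 0.702 |
| 4.1 / 2.5 | 1.64 | 0.711 | 0.711 |
| 4.0 / 2.0 | 2.0 | 0.720 | 0.719 |
| 3.0 / 1.0 | 3.0 | 0.738 | 0.735 |
| 4.5 / 1.5 | 3.0 | 0.744 | 0.741 |

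**Step 4: precision, power and type I error.** Simulated trials had 60 clusters, 10 children per cohort per cluster, gamma cluster variation with CV 0.44 and no dropout. Each data set was fitted with a cloglog mixed model with a cluster random intercept, once without and once with a cohort term. There were 4000 data sets per row, and rejection meant z < −1.678 at a single look.

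| Hazards, true HR | HR without / with | Mean SE without / with | Rejected without / with |
|---|---|---|---|
| 4.1 / 2.5, 0.70 | 0.712 / 0.702 | 0.126 / 0.132 | 83.6% / 83.7% |
| 4.0 / 2.0, 0.70 | 0.721 / 0.702 | 0.123 / 0.132 | 84.1% / 83.7% |
| 4.5 / 1.5, 0.70 | 0.742 / 0.700 | 0.113 / 0.133 | 82.9% / 83.2% |
| 4.0 / 2.0, 1.00 | 1.002 / 1.002 | 0.122 / 0.132 | 4.6% / 4.5% |

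The Monte Carlo error on each power figure is about 0.6 points, and the paired comparison is tighter. At hazards 4.0/2.0 the two models disagreed in only 86 of 4000 data sets, 50 one way and 36 the other. The pooled estimate shrinks, but its standard error shrinks with it, so the test statistic hardly moves.

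**The case against.** **The effect is small and conditional.** This stands. At a ratio of 1.64 the shift on the log scale is ln(0.711/0.70) = 0.016, about an eighth of the design SE of 0.129. It is toward no effect, so it cannot create a false claim of efficacy. No year-to-year ratio comes from the protocol.

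**The detail may sit in the statistical analysis plan.** This stands in part. The covariate list is left open, and the article does not say whether visit numbering restarts for cohort 2. Numbering that ran through all 24 months would absorb year. Against that, the article itself places year among the terms added for a supplementary analysis, so the natural reading is that the primary model lacks it.

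**The supplementary analysis already shows year-specific PE.** True, and readers would see any gap there. The primary estimate would still carry the dilution.

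**Two stronger readings are tempting, and neither is supported.** A reader might infer that the trial loses power. Putting 0.7114 or 0.7204 into the power formula with the SE held at 0.1292 gives 83.1% or 80.5%, against 86.0% at 0.70. Holding the SE fixed is the mistake: about 77% of that variance (0.01291/0.01670) is between-cluster variation, which the omitted term compresses along with the treatment effect. Step 4 shows no material loss. A reader might also extend the argument to overall infections. The mechanism is depletion by first infections, and that model keeps children at risk and has a child-level random effect. Nothing here shows a bias in it.

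**Conclusion.** The point holds as a minor one. As the article reads, the primary first-infection model has no cohort or year term, although the protocol expects the years to differ. If they do, PE is understated in one direction: a true 30% becomes about 29% at a year-to-year hazard ratio of 1.64, 28% at 2.0 and about 26% at 3.0. If the years are alike there is no bias. The sizes rest on the assumed ratios, on equal cohorts and on visit numbering that restarts with each cohort. The stated 85% power and the type I error rate are not challenged, and no claim is made about the overall-infection model.

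**What to change.** In the primary first-infection model, add cohort (year 1 or 2) as a fixed effect, or let each cohort have its own set of visit baseline hazards. Do the same in the covariate-free version, so that treatment remains the only substantive covariate there. Keep the year-by-treatment interaction as the supplementary analysis. If the analysis plan already does this, one clause in the protocol saying so is enough.

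The cost is one nuisance parameter for a main effect, or about 13 for separate baselines with four-week visits, against roughly 1000 events. The main effect was the version simulated, and it removed the bias with no material change in power or type I error. No new data are needed. The change should be fixed before anyone sees results by arm.

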#### Statistical methods—secondary endpoints

##### PE of SR protection against the overall malaria infections

The secondary hypothesis on PE against overall new malaria infections will be tested by comparing hazard rates of the overall malaria infection between the SR and placebo arms in the ITT population using a similar approach as for the first-time infection with an additional random effect term to account for the dependency among the multiple malaria incidences collected from the same individual.

##### PE analysis without baseline covariates

A PE analysis on the first-time and the overall infections will be also performed by removing all the baseline covariates from the cloglog models and keeping “intervention group” as the only covariate (in addition to visit, as a categorical predictor per the model assumptions and setup). The hazard ratios between SR and placebo will be provided, along with 2-sided 90% CIs.

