## Assignment of interventions: Allocation

### Sequence generation {16a}

For the baseline cohort, recruitment of participants for enrolment was based on random selection of HHs using census mapping of the study area. Random allocation of clusters into treatment assignment will be performed during baseline following interim analysis of incidence and prior to cohort 1 participant enrolment. Baseline estimates of incidence will be used to guide decisions on cluster stratification. A total of 60 clusters (30 per treatment arm) will be randomly allocated to receive either the SR intervention or placebo treatment. The cluster allocation sequence will be generated by the external statistician serving on the Data Safety Monitoring Board (DSMB) using a random number generator (https://www.random.org).

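### If clusters are allocated within baseline-incidence strata, the covariate-free PE analysis as worded drops the stratum, and its 90% confidence intervals become conservative

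*Protocol article*

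**What the plan says.** Three places in the protocol article bear on this.

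- **Sequence generation {16a}.** Clusters are allocated during the baseline phase, after an interim look at incidence. "Baseline estimates of incidence will be used to guide decisions on cluster stratification". No strata are defined, and the text then describes a random allocation of 60 clusters, 30 per arm.
- **Statistical methods, primary endpoint.** "The model will include the treatment arm (SR vs. placebo), relevant baseline covariates, and a random effect" for cluster. The paragraph before lists cluster-level baseline infection incidence among the characteristics to be summarised by arm.
- **PE analysis without baseline covariates**, under secondary endpoints. First-time and overall infections are re-analysed by "removing all the baseline covariates from the cloglog models and keeping “intervention group” as the only covariate", besides visit as a categorical term. Hazard ratios with two-sided 90% confidence intervals are reported. No test or decision rule is attached, and nothing says that the cluster random effect is removed.

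**The concern.** A stratum built from baseline incidence is itself a baseline covariate. An instruction to remove all of them and keep only intervention and visit therefore excludes it, if it exists.

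Stratified allocation balances the arms on the stratum, so variation between strata no longer contributes to the true sampling variance of the log hazard ratio. A model without the stratum does not know this. It leaves that variation in the cluster random effect and charges it to the treatment contrast. Keeping the random effect does not cure the problem, because that is where the excess error sits.

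At stake is the accuracy of the intervals in a planned, reported analysis of both infection endpoints. The unadjusted and adjusted results could differ in apparent precision partly because one model ignores how clusters were allocated.

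**Working it through.** **Inputs from the article:** hazard ratio 0.70; between-cluster CV 0.44; 30 clusters per arm; 1055 first-time events; baseline hazard 3.0 per person-year; one-sided alpha 5%, with a final boundary of 0.04668; baseline cohort of 20 core and 14 buffer children per cluster, followed for 4 months.

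**Assumed, because the article gives no value:** how strongly baseline incidence predicts a cluster's rate at follow-up; the number of strata; and the baseline events per cluster available when strata are formed.

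**1. Reproduce the design.** The article states that "1055 first-time malaria events will need to be observed to reach 85% power".

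- Var(log HR) = 4/1055 + 2 × 0.44²/30 = 0.0038 + 0.0129 = 0.0167, so SE = 0.129.
- |ln 0.70|/SE = 0.357/0.129 = 2.76.
- Power = Φ(2.76 − 1.645) = 86.8% at alpha 0.05, 86.0% at the final boundary, and 86.3% with both looks. This agrees with the stated 85% to within 2 points.
- Between-cluster share of the variance: 0.0129/0.0167 = 77%. This is the part that a baseline-incidence stratum can reduce.

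**2. Upper bound by formula.** Let R² be the share of between-cluster variance that the strata remove. Under stratified allocation the true variance is 4/1055 + 2 × 0.44² × (1 − R²)/30, while the model without the stratum still reports 0.0167. The reported 90% half-width is 1.645 × 0.129 = 0.213 on the log scale, or 0.566 to 0.866 around a hazard ratio of 0.70.

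| R² (assumed) | Half-width with stratum | Reported ÷ needed | Coverage of reported CI |
|---|---|---|---|
| 0 | 0.213 | 1.00 | 90.0% |
| 0.25 | 0.191 | 1.11 | 93.3% |
| 0.50 | 0.166 | 1.28 | 96.4% |
| 0.75 | 0.138 | 1.54 | 98.9% |

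This bounds the effect from above, because a few strata cut from noisy baseline counts remove less variance than the underlying baseline rate would.

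**3. Simulation with two or three strata cut from simulated baseline counts.** Cluster log-rate variance is ln(1 + 0.44²), follow-up sampling variance 1/18 per cluster, baseline counts are Poisson, and intervals are t-based. Two assumptions on baseline information:

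- All children, the full 4 months, no losses: 34 × 4/12 × 3.0 = 34 events per cluster.
- Core children only, an assumed 2 months: 20 × 2/12 × 3.0 = 10 events per cluster.

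| Correlation (assumed) | SE excess, 34 events | Coverage | SE excess, 10 events | Coverage |
|---|---|---|---|---|
| 0.5 | 6–7% | 91–92% | 4–5% | 91–92% |
| 0.7 | 12–16% | 93–94% | 8–11% | 93% |
| 0.9 | 23–31% | 96% | 15–20% | 95% |

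A repeat run agreed with these figures within simulation error, and the low end can fall to about 3%. In the 34-event runs, coverage with the stratum in the model was 89–90%.

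**4. Without stratified allocation.** A separate simulation of simple random allocation gave coverage of 0.907, 0.900 and 0.905 for the unadjusted interval at R² = 0.25, 0.50 and 0.75. The interval is then valid.

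**The case against.** The strongest reply is that the premise is hypothetical. The article says only that baseline incidence will inform decisions on stratification. It adopts no strata, and without them the interval does what it claims. That stands, and it is why the point is conditional.

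Second, the analysis is unadjusted by design. Its heading says so, it carries no decision rule, and any error is towards caution. This also stands and sets the severity. It does not remove the point, because an unadjusted analysis discards optional covariates, whereas an allocation stratum is part of the design.

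Third, the primary model has room for baseline incidence, which the article already lists as a cluster characteristic. Naming the exact covariates is ordinary analysis-plan content. This stands too: the primary-endpoint section is not at fault for leaving the stratum unnamed.

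A reader might infer more: that the 90% intervals are too wide in any event, that the trial loses power, or that intervention is literally the only model term. The documents support none of these. Over-width needs both stratified allocation and a prognostic stratum. The decision rule concerns the primary hypothesis, which is tested in a different model. Visit is kept, and the random effect is not said to go.

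**Conclusion.** The point holds conditionally and is minor. If clusters are allocated within baseline-incidence strata, the covariate-free analysis as worded omits the stratum and its 90% intervals are conservative. For an assumed baseline-to-follow-up correlation of 0.5 to 0.9, the standard error is about 3% to 30% too large and coverage is about 91% to 96%, varying with the number of strata and the baseline events per cluster. If allocation is not stratified, there is no error. False-positive risk is not raised, and the primary test, its alpha and the stated 85% power are untouched.

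**What to change.** Reword the section on PE analysis without baseline covariates conditionally: if clusters are allocated within strata, the model keeps intervention group, visit, the cluster random effect and the allocation stratum, and removes only the other baseline covariates. For consistency, count the same stratum, or log baseline cluster incidence, among the baseline covariates of the primary model. If allocation turns out not to be stratified, the present wording can stay.

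The cost is a sentence of text and one or two degrees of freedom out of 58 (60 clusters less two arms) for two or three strata. No new data are needed.

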##### Diversion effect

To assess the diversion effect on the first and overall malaria infections, similar models as the cloglog models used for analyzing the primary and secondary endpoints of the first-time and overall infections will be applied, with additional covariate terms to account for the distance of each HH in the buffer zone to the boundary of the core area. The difference in the malaria first-time and overall hazard rates in the buffer zones between the SR and placebo arms at different distances to the core area will be quantified.

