### Objectives {7}

The study’s primary objective is to demonstrate and quantify the protective efficacy (PE) of the Mosquito Shield™, a transfluthrin-based SR product, in reducing the incidence of malaria infection in humans.

Secondary objectives will address issues related to the optimization and application of SR products for public health and confirm the range of contexts within which SR PE can be achieved. Secondary objectives are:
To estimate the total number of infections averted due the SR intervention by comparing the number of infections per person per year in intervention and control arms over the 2-year follow-up period;To investigate whether the SR intervention induces diversion of mosquitoes from within intervention areas to locally unprotected individuals thereby having a differential impact on infection incidence among protected and locally unprotected individuals;To measure the impact of the SR intervention on entomological correlates of transmission (e.g., vector densities, mosquito infection, host seeking/biting and parity rates) to set benchmark thresholds and streamline future intervention trials with other SR products by measuring those endpoints correlated to PE.

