#### Description of study clusters

The unit of randomization for the intervention will be a cluster. A total of 60 clusters will be delineated for the trial (Fig. 1). A cluster is defined as a core area, where the SR or placebo will be implemented, plus an untreated buffer zone where diversionary effects of the Mosquito Shield™ will be measured. The core areas of each cluster will be discrete villages. In the Health and Demographic Surveillance System maintained by KEMRI and CDC in neighboring Siaya County, the average village has 103 compounds in an area of 1.75 km^2^. Compounds are defined as family units with one or more structures plus surrounding farmland. A typical family compound has 5.5 HH members. Therefore, an average population size for a village in this area is estimated to be 567 inhabitants. Pre-trial census data will be used to delineate cluster boundaries based on number of HHs and inhabitant age groups such that each cluster will have at least one anticipated child meeting the inclusion criteria for assurances of sample size requirements.

For the buffer zones, mapping will extend approximately 300–500 m from the border of each cluster core area. Assuming core areas are approximately round with an area of 1.75 km^2^, this will result in a radius of 0.75 km. Extending a buffer zone 300 m around the core area will result in a radius of 1.05 km, and extending a buffer zone 500 m will result in a radius of 1.25 km. Estimating the total area including the buffer zones and then subtracting out the area of the core area results in areas of 1.7 km^2^ and 3.1 km^2^ for buffer zones of 300 m and 500 m respectively. Typically, HHs are randomly distributed in the landscape of western Kenya and it is therefore expected that a 300 m buffer zone of 1.7 km^2^ should have a similar number of HHs as the core areas which are estimated to have an area of 1.75 km^2^. Final determination of the buffer zones will be based on mapping and the actual number of HHs required to meet the sample size of 40 HHs per cluster for the analysis of SR diversionary effects. Because the buffer zones will extend into neighboring villages, we will map approximately 100–150 villages and then select villages as core areas based on feasibility of including a 300–500 m buffer around 60 of them.

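### The diversion model adjusts only for distance to the core area, although the plan's own areas leave placebo-buffer homes liable to lie near another cluster's SR core

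*Protocol article*

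**What the plan says.** One secondary objective (Objectives {7}) is "To investigate whether the SR intervention induces diversion of mosquitoes from within intervention areas to locally unprotected individuals". Under Cohort follow-up, buffer homes receive neither product. Under Diversion effect, hazards in SR and placebo buffers are contrasted with cloglog models like those for the main endpoints, "with additional covariate terms to account for the distance of each HH in the buffer zone to the boundary of the core area". Placebo-buffer homes are therefore the unexposed reference.

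Description of study clusters sets the geometry:
- For the neighbouring county, "the average village has 103 compounds in an area of 1.75 km^2".
- "Assuming core areas are approximately round with an area of 1.75 km^2^, this will result in a radius of 0.75 km".
- Subtracting the core "results in areas of 1.7 km^2^ and 3.1 km^2^ for buffer zones of 300 m and 500 m respectively".
- The plan is to "map approximately 100–150 villages and then select villages as core areas based on feasibility of including a 300–500 m buffer around 60 of them".
- "Final determination of the buffer zones will be based on mapping and the actual number of HHs required to meet the sample size" of 40 households per cluster.

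Mapping of the study area and baseline measurements says that the buffers reach into adjoining villages, and that this is why so many villages are mapped. Sequence generation {16a} allocates 30 clusters to each arm at random. Stratification guided by baseline incidence is mentioned, but no spatial constraint.

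**The concern.** The reference group is clean only if placebo-buffer homes have no SR core within the range over which diversion might act. The article states no minimum distance between a placebo buffer and an SR core and no ban on overlapping buffers, and its model has no term for the SR core of another cluster.

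If some reference homes receive diverted mosquitoes, the SR/placebo hazard ratio can be pulled towards 1. For a question about harm to non-users, that is the falsely reassuring direction. The profile by distance could be distorted too, because placebo homes farthest from their own core tend to be those nearest another core.

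**Working it through.** **1. Reproduce the stated areas.** With core radius 0.75 km, the buffer area is π[(0.75 + b)² − 0.75²]. For b = 0.3 km this is 3.464 − 1.767 = 1.70 km². For b = 0.5 km it is 4.909 − 1.767 = 3.14 km². Both agree with the stated 1.7 and 3.1.

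**2. Area budget.**
- Needed with 300 m buffers: 60 × (1.75 + 1.7) = 207 km², and 207/1.75 = 118.3, so about 119 villages.
- Needed with 500 m buffers: 60 × (1.75 + 3.1) = 291 km², and 291/1.75 = 166.3, so about 167 villages.
- Mapped: 100 × 1.75 = 175 km² to 150 × 1.75 = 262.5 km².

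Circles cover at most 0.9069 of a plane, so separate 300 m buffers need about 118.3/0.9069 = 130.4, or 131 villages. At 500 m, overlap is forced over the whole mapped range. At 300 m it is forced below about 119 villages (131 if clusters are round) and avoidable above that.

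**3. Share of placebo-buffer homes within the buffer width of an SR core.** Three layouts were tried: SR cores scattered independently, with share 1 − exp[−30/(1.75V) × buffer area] for V villages; a hexagonal lattice of 1.75 km² villages without edges and 60 cores picked at random; and the same lattice with cores spread to minimise adjacency. The lattices use 30:30 random allocation.

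| Villages | Buffer | Needed/mapped | Scattered | Lattice, random | Lattice, spread |
|---|---|---|---|---|---|
| 100 | 300 m | 207/175 = 1.18 | 25.2% | 23.9% | 25.5% |
| 100 | 500 m | 291/175 = 1.66 | 41.6% | 31.9% | 40.2% |
| 150 | 300 m | 207/262.5 = 0.79 | 17.6% | 15.3% | 6.5% |
| 150 | 500 m | 291/262.5 = 1.11 | 30.2% | 21.0% | 10.4% |

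Off the lattice, 300 m buffers with about 131 or more villages and deliberate spacing can reach 0%. Even then, where two 300 m buffers touch, a home at that point is 300 m from the other core, so it is not clear of a 500 m range.

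**4. Effect on the hazard ratio.** The documents give no diversion effect, so a true ratio of 1.20 (d = 0.20) is assumed. Let f be the exposed share of placebo-buffer homes.

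*One SR core gives the full effect:* observed HR = 1.20/(1 + 0.20f).
- f = 18%: 1.20/1.036 = 1.158
- f = 25%: 1.20/1.05 = 1.143
- f = 40%: 1.20/1.08 = 1.111

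The loss on the log scale is 0.035 at 18% and 0.077 at 40%, that is 19% and 42% of ln 1.20 = 0.182. A protective spill-over of 0.80 also moves towards 1: 0.80/0.964 = 0.83 and 0.80/0.92 = 0.87.

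*Effects add across SR cores:* SR-buffer homes gain from neighbouring SR cores too, in proportion 29/59 against 30/59 for placebo buffers. At f = 30% the SR-buffer share is 0.30 × 29/30 = 0.29. The observed HR is (1 + 0.20 + 0.29 × 0.20)/(1 + 0.30 × 0.20) = 1.258/1.06 = 1.19. The rate difference is then 0.20 × (1 + 0.29 − 0.30) = 0.198 of the unexposed rate against a true 0.20, so almost unbiased.

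**The case against.** The strongest reply is that the layout is not known from the text. Fig. 1, which maps the clusters, was not available for this check. The areas are planning approximations: a mean village size from another county, round cores, and villages that fill the land. Choosing core villages on the feasibility of fitting a buffer may itself be a spacing rule. A 300 m buffer is expected to hold about as many households as a core, and the average village has 103 compounds against 40 households needed, so 500 m everywhere is a worst case. All of this stands, and it is why the share is given as a range that starts at 0%.

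Second, the dilution in the first calculation of step 4 needs one SR core to saturate exposure. The documents neither support nor refute that. This also stands.

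Third, the consequence is limited. Quantification of diversionary effect sets no formal hypothesis and states a 90% half-width of 0.220 on the log scale, so even the larger loss of 0.077 is about a third of it (0.077/0.220 = 0.35). That is correct, but the bias is systematic and would not shrink with more data.

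Fourth, exact exposure coding may sit in the analysis plan. That answers the question of coding detail. It does not remove the point that the protocol itself names the distance covariate, and on the natural reading that covariate does not measure exposure for homes near another cluster's SR core.

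**Conclusion.** The contrast and covariate as written do not protect the diversion estimate against SR exposure among placebo-buffer homes, and the stated areas make some such exposure plausible: forced overlap at 500 m, and overlap over much of the 300 m range. The exposed share is 0% to about 40%, depending on layout. For an assumed true ratio of 1.20, the observed ratio is about 1.16 to 1.11 at 18% to 40% exposed under saturation, and about 1.19 at 30% exposed if effects add.

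A reader might infer that many placebo-buffer homes are in fact exposed and that the estimate is therefore biased towards no diversion. The documents do not support that: actual overlap cannot be read from planning averages, deliberate spacing is possible, and the size of any bias turns on an unknown exposure mechanism.

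The conclusion assumes that the named core area is the home's own, that cores are round and of average size, that homes are evenly spread, that buffers lie within the mapped villages, and that diversion is equal anywhere within range. It concerns a secondary estimate, and no test decision depends on it.

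**What to change.** In the Diversion effect section, state whether buffers may overlap. From the mapped GPS coordinates, compute for every buffer home in both arms, whichever cluster recruited the child, the distance to (or number within 500 m of) SR cores, and the same for all cores. Add these terms to the cloglog diversion model. The all-cores term matters because, given how many cores are nearby, the number that are SR depends on the randomisation. For isolated homes the SR-proximity term and the arm term carry the same information, so the text should say which coefficient or combination is the diversion estimate.

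Keep all homes in the main estimate. Add a sensitivity analysis that excludes, by the same rule in both arms, homes within 500 m of any other cluster's core, and report the number of such homes by arm. Do this after unblinding, with no change to recruitment.

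Two alternatives should be avoided. Choosing buffer homes by distance from opposite-arm cores would make recruitment depend on allocation and could threaten blinding. Dropping only placebo-buffer homes near SR cores would be an asymmetric post-randomisation exclusion.

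The cost is one GIS calculation on coordinates the trial already plans to collect, a little more analysis, and a wider interval in the sensitivity analysis.
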